**Statistical Analyses**

The sample size is calculated with a power analysis and is aimed at our main study outcome, AL. From literature, we know that approximately 10% of all colorectal patients receiving an anastomosis will develop AL [14,37]. The aim of the study is to detect significant and clinically relevant differences between the AL group and the non-AL group. Therefore, we used data from a previous study undertaken by our group to determine sample size [20]. We chose our least significant finding, to avoid the study being underpowered. Based on an effect size of 0.41 (calculated with mean calprotectin levels and SD on day 1), with a power of 0.80 and a 95% confidence interval, the total sample size will be 560, of whom an estimated 51 patients will develop AL. Assuming a 5% dropout rate, the total number of patients that needs to be included in this study is 588.

After data collection, normality will be tested by the D’Agostino-Pearson test. Student’s t-tests will be used for between-group comparisons for continuous data. Dichotomous variables will be compared using Pearson’s chi-squared test. All data will be presented as mean and standard error of the mean. The area under the curve of receiver operating characteristic (ROC) curves will be used to calculate the diagnostic ability of the studied markers predicting AL. The area under the ROC curve is a summary measure of accuracy, lying in the range from 0.5 to 1, with 1 indicating perfect discrimination and 0.5 indicating no discrimination capacity. To determine the most ideal combination of markers, logistic regression analyses will be performed.

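### Student's pooled t-test is fixed for every continuous marker in groups of about 51 and 509, so single-marker p-values are unreliable if spread differs between groups, and power is lost on strongly skewed markers

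*Protocol article*

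**What the plan says.** All of the relevant text is in the Statistical Analyses section of the protocol article.

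- The normality step: "After data collection, normality will be tested by the D’Agostino-Pearson test". The text does not say what follows if normality is rejected.
- The test itself, with no condition attached: "Student’s t-tests will be used for between-group comparisons for continuous data". No unequal-variance test, rank test or transformation is named.
- The summary: "All data will be presented as mean and standard error of the mean".
- The sizing, which is itself a two-group comparison of means. The effect is a standardised difference of 0.41, taken from day-1 calprotectin, at 80% power and 95% confidence. The result is given as "the total sample size will be 560, of whom an estimated 51 patients will develop AL".

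The same section gives diagnostic ability to the area under the ROC curve and the combination of markers to logistic regression. Study Outline lists the plasma markers (I-FABP, citrullin, calprotectin, smooth muscle protein 22, CRP, leukocyte count), drawn before surgery and on days 1, 3 and 5.

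**The concern.** Student's t-test estimates one common variance. With ten times as many non-leak as leak patients, that estimate is almost entirely the non-leak variance, while the uncertainty in the difference comes mostly from the small leak group. If leak patients vary more, the standard error is too small and too many markers are declared different.

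The article gives some reason to expect this after surgery. Its Introduction describes presentations from mild symptoms to severe sepsis, with diagnosis from day 3 to beyond day 30. Study Outline counts abscesses near the anastomosis as leaks and records subclinical leaks. On days 3 and 5 the leak group could therefore mix patients who are already inflamed with patients who are not.

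A second issue is scale. Plasma concentrations may be right-skewed, and a test of raw means is then inefficient. At stake is the reliability of the statements that a given marker differs between leak and non-leak patients, which the article names as the aim behind its sample size.

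**Working it through.** **Inputs from the article.** Effect size 0.41, power 0.80, 95% confidence (read as two-sided 5%), 560 patients, 51 with leakage, hence 560 − 51 = 509 without.

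**Inputs assumed, because the article gives none.** Ratio of leak to non-leak SD from 0.5 to 3; SD of the log concentration from 0.5 to 1.5.

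**Step 1: reproduce the plan's power.** With equal variances the noncentrality is 0.41 / sqrt(1/51 + 1/509) = 0.41 / sqrt(0.02157) = 2.79. Power is about Φ(2.79 − 1.96) = 0.797, or 0.796 from the noncentral t. The stated 80% reproduces, and it presumes equal variances. A one-sided test would give 0.874, so the two-sided reading fits.

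**Step 2: type I error under unequal spread.** Set the non-leak SD to 1 and the leak SD to r.

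- Variance the pooled test uses: [(50r² + 508) / 558] × (1/51 + 1/509)
- True variance of the difference: r²/51 + 1/509
- Type I error ≈ 2 × [1 − Φ(1.96 / f)], where f is the square root of true over pooled variance

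At r = 2 the pooled variance is (708/558) × 0.02157 = 0.0274 and the true variance is 4/51 + 1/509 = 0.0804. So f = sqrt(0.0804/0.0274) = 1.71, and the error is 2 × [1 − Φ(1.96/1.71)], about 25%.

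Simulation with normal data, equal means and 40,000 runs per ratio:

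| SD ratio, leak / non-leak | Student, formula | Student, simulated | Welch, simulated |
|---|---|---|---|
| 0.5 | 0.08% | 0.06% | 5.0% |
| 1 | 5.0% | 5.1% | 5.1% |
| 1.25 | 10.2% | 10.3% | 5.1% |
| 1.5 | 15.7% | 15.3% | 5.0% |
| 2 | 25.3% | 25.4% | 5.0% |
| 3 | 37.2% | 37.5% | 5.0% |

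**Step 3: power on skewed markers.** Lognormal values, a shift of 0.41 SD on the log scale, 4,000 runs per setting:

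| Log-SD | Student on raw values | Student on log values |
|---|---|---|
| 0.5 | 0.77 | 0.78 |
| 0.75 | 0.74 | 0.80 |
| 1.0 | 0.66 | 0.81 |
| 1.25 | 0.57 | 0.80 |
| 1.5 | 0.49 | 0.79 |

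With no true difference, the raw-scale Student test keeps 4.9-5.9% in these settings. Skew alone therefore does not inflate its error; unequal spread does.

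**Step 4: check the alternatives.**

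- Welch on raw skewed values is not adequate. At log-SD 1.0 its type I error is 8.5% and its power 0.46.
- Mann-Whitney does not protect against unequal spread. With normal data, equal centres and SD ratios of 1.25, 1.5, 2 and 3, its rejection rate is about 7.5%, 10%, 13% and 16%.

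**The case against.** **The inflation rests on an assumed SD ratio.** This stands. At a ratio of 1 the test is correct, and below 1 it is conservative. The sepsis argument cannot reach the pre-operative samples, which serve the primary aim. It is also weak for day 1, since the Introduction puts diagnosis at day 3 or later, with a mean of 12.7 days.

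**Equal means with unequal spread is a narrow null.** This stands in part. For skewed concentrations spread tends to rise with the mean, so a larger leak-group SD would often come with a real difference. A marker with the same distribution in both groups keeps close to 5%.

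**The power loss is partly an artefact of scale.** This stands in part. The plan's 0.41 comes from a mean and SD, so it is a raw-scale figure. A 0.41 shift on the log scale is only about 0.37 on the raw scale at log-SD 1.0. With the raw effect held at 0.41 and a multiplicative shift, Student's power is about 67-74% over log-SD 0.5 to 1.2; for a pure location shift it is 79-82%. A reader might infer that the stated 80% power is simply not achieved. The article does not support that, because it gives no information on skewness.

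**The article is condensed, and a fallback may follow the normality test in the full plan.** It may, and its absence here is not the point. The point is the sentence that is present, which names one test for all continuous data. Even a fallback triggered by non-normality would leave unequal variance unaddressed.

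**Conclusion.** The concern holds, conditionally. The article fixes a test whose error rate depends on equal spread in groups of 51 and 509. If leak patients are more variable, which is most plausible on days 3 and 5, per-marker type I error is about 10%, 15% and 25% at SD ratios of 1.25, 1.5 and 2. For strongly skewed concentrations the raw-scale test has roughly 65-70% power at log-SD 1.0, against about 80% on the log scale; at log-SD 0.5 the difference is trivial. The SD ratios and log-SDs are assumptions throughout.

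A reader might go further and infer that false-positive t-tests decide which markers enter the risk algorithm. The article states no such step: ROC curves and logistic regression do that work, and neither uses a pooled variance. The effect is confined to statements about single markers. This makes it a cheap and worthwhile improvement, not an error that must be cured before the study can be relied on.

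**What to change.** Replace the t-test sentence with a rule fixed before the group comparisons are run:

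- Plasma concentrations expected to be right-skewed are named in advance and log-transformed by that rule, not according to the D'Agostino-Pearson result.
- Continuous comparisons use Welch's unequal-variance t-test, on the log scale for those markers and on the original scale for roughly symmetric ones.
- Welch's test is not applied to raw skewed values, and Mann-Whitney is not offered as protection against unequal spread.

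The cost is one sentence of wording and about one point of power if the variances are in fact equal. No further patients, samples or data are needed, and the ROC and logistic regression plans stay as they are.

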## Methods

This is a study protocol for a multicenter, prospective observational study. This study is approved by the Medical Ethical Committee of the Maastricht University Medical Centre. A written informed consent is required from all participating patients and the trial will be conducted in compliance with the rules of *Good Clinical Practice*.

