### Study Population

All patients aged >18 years undergoing elective colorectal surgery for colorectal carcinoma, with the construction of an anastomosis, in one of the three participating centers are eligible for inclusion. Patients with large adenomas (large tubular, tubulovillous, or sessile) that cannot be resected radically by means of endoscopy will be included as well, provided that the adenoma is removed surgically with the construction of a colorectal anastomosis. Sample size analysis revealed that 588 consecutive patients have to be included at the outpatient department, prior to surgery. Patients undergoing colorectal surgery for benign conditions, those with permanent stomata without anastomosis, or patients that are unable to give informed consent will be excluded from participation in this study, as well as pregnant patients. If no anastomosis is constructed during surgery, the patient will be withdrawn from the study. Eligibility for inclusion will be determined during a visit at the outpatient department. Upon approval, the patient will receive oral and written information regarding the study, after which he/she will have ample time to reconsider participation. Informed consent will be signed in the presence of the surgeon or researcher.

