Upon hospital admission, a buccal swab will be performed in order to collect DNA to screen for MBL and COX-2 polymorphisms. In addition, composition of volatile organic compounds (VOCs) in exhaled air will be measured both pre- and post-operatively. Various metabolic processes produce markers that are released into the circulation and, upon passage through the pulmonary system, can be identified as volatile products in exhaled air. The occurrence of (chronic) inflammation and/or oxidative stress can result in the excretion of volatile compounds that generate unique VOC patterns [32]. Furthermore, several baseline characteristics will be acquired prior to surgery, and stool will be collected on three occasions (pre-operatively, post-operatively and at the outpatient department during a control visit) in which the intestinal microbiome can be identified. It has been suggested that the microbiota play an important role in the pathogenesis of AL [33] and that the composition of the intestinal flora can be altered by surgical stress [34]. Plasma will be collected prior to surgery and on post-operative days 1, 3, and 5, in order to determine the concentration of markers for enterocyte damage (eg, I-FABP, citrullin, and calprotectin), transmural ischemia (eg, smooth muscle protein 22), and general inflammation markers (eg, CRP and leukocyte count).

In addition, SNAQ and Malnutrition Universal Screening Tool scores are obtained to assess the nutritional status of the patient, and CT-images are analyzed for total skeletal muscle cross-sectional area in order to distinguish sarcopenic patients from those in good nutritional health [25]. Generalized atherosclerosis will be assessed using abdominal CT-scans, as this is a proposed risk factor for AL [35,36]. Finally, a tissue sample will be obtained from the resected specimen, on which conventional and immunohistochemical staining will be performed.

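### The single-marker t-tests, chi-squared tests and ROC areas carry no centre term, so they are biased if leak rates and marker levels differ between the three centres in an aligned way

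*Protocol article*

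**What the plan says.** The Methods section opens with "This is a study protocol for a multicenter, prospective observational study". Under Study Population, patients operated on "in one of the three participating centers are eligible for inclusion". Nothing is randomised.

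The Statistical Analyses section names four tools:
- For continuous markers, "t-tests will be used for between-group comparisons for continuous data".
- For binary markers, "Dichotomous variables will be compared using Pearson" (the chi-squared test).
- ROC areas "will be used to calculate the diagnostic ability of the studied markers predicting AL".
- Last, "To determine the most ideal combination of markers, logistic regression analyses will be performed".

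No stratum, covariate or centre term is attached to the first three. The logistic regression is named without a covariate list, so centre is neither included nor excluded there. The article does not describe its comparisons as pooled or unadjusted. That is simply what a two-sample t-test and a Pearson chi-squared test are as named.

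The markers include some that could plausibly depend on the place of collection. The Study Outline says that "composition of volatile organic compounds (VOCs) in exhaled air will be measured both pre- and post-operatively", and adds stool microbiome and plasma markers.

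**The concern.** A two-sample comparison of leak with non-leak patients answers the intended question only if centre is not tied to both sides of it. Leak rate may differ between hospitals through case mix and technique; the Discussion itself refers to technical factors that help predict leakage. Breath, stool and plasma values may differ between hospitals through local collection and handling. If the two sets of differences run in parallel across the three centres, the t-test, the chi-squared test and the overall ROC curve register part of the centre difference as a marker difference. If they run in opposite directions, a real marker may be masked.

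Many markers are to be screened with about 51 leaks, and the aim is an individual risk estimate that informs decisions on anastomosis and ostomy. A marker that partly identifies a hospital is a poor candidate for that use.

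**Working it through.** **The plan's own figure.** The design rests on "Based on an effect size of 0.41 (calculated with mean calprotectin levels and SD on day 1"), 80% power and a 95% confidence level, read as two-sided alpha 0.05. With one leak per ten non-leaks:

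n(leak) = (1 + 1/10) × ((1.960 + 0.842)/0.41)² = 1.1 × 46.7 = 51.4, so the total is 11 × 51.4 ≈ 565.

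The article gives 560 with 51 leaks, for which the power is 0.797. The figure reproduces, and the calculation is a plain two-group one without centre.

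**Bias when centre is left out.** Inputs:
- N = 560 and three centres: from the article.
- Equal centre sizes: assumed.
- Within-centre marker SD of 1 and no marker effect within any centre: assumed, to isolate the artefact.
- Centre leak rates 8/11.5/15%: assumed. They span the 8-15% literature range in the Introduction, which is not a range between these centres.
- Centre marker means −s, 0, +s with s = 0.3, 0.5 or 0.8 SD: assumed.

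Worked case, s = 0.5:
1. Overall leak rate: (0.08 + 0.115 + 0.15)/3 = 0.115, i.e. 64.4 leaks and 495.6 non-leaks.
2. Centre shares among leaks: 0.08/0.345, 0.115/0.345, 0.15/0.345 = 0.232, 0.333, 0.435. Among non-leaks: 0.92/2.655, 0.885/2.655, 0.85/2.655 = 0.347, 0.333, 0.320.
3. Spurious mean difference: 0.5 × (0.435 − 0.232) − 0.5 × (0.320 − 0.347) = 0.115.
4. The pooled SD, including between-centre spread, is 1.080, so d = 0.115/1.080 = 0.106.
5. SE = 1.080 × √(1/64.4 + 1/495.6) = 0.143, so the expected z is 0.80.
6. False-positive rate = P(Z > 1.96 − 0.80) + P(Z < −1.96 − 0.80) ≈ 0.123 + 0.003 = 0.126.

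The same steps for the other shifts:

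| Shift between successive centres | Spurious d | AUC | False-positive rate (nominal 5%) |
|---|---|---|---|
| 0.3 SD | 0.07 | 0.519 | 8.0% |
| 0.5 SD | 0.11 | 0.530 | 12.6% |
| 0.8 SD | 0.15 | 0.545 | 21.3% |

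Simulated studies with 187/187/186 patients agree, at about 8 to 23% across runs. With centre as a covariate the same simulations return about 5%.

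**When the bias vanishes.** With leak rates equal at 10% in all centres, the centre shares are the same in both groups. Then d = 0, AUC = 0.500 and the error is 5.0% whatever the shift. With rates 8/11.5/15% but marker means +0.5, −0.5, +0.5, the difference is 0.5 × (0.232 − 0.333 + 0.435) − 0.5 × (0.347 − 0.333 + 0.320) = 0, and the error is again 5%.

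**Sensitivity to the assumed values.** Narrower leak rates of 8/10/12% with a total marker gap of 0.5 to 1.0 SD give 5.8 to 7.8%. Rates of 8/8/15% with a 1 SD gap give 13.4%, d = 0.12 and AUC 0.533. Rates of 5/9/14% with s = 0.3 to 0.8 give about 11 to 37%, but 5% lies below the article's 8-15% range and s = 0.8 means a 1.6 SD gap between the extreme centres.

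**Cost of adjusting.** For 8/11.5/15%, centre explains (2 × 0.035²/3)/(0.115 × 0.885) = 0.8% of the variance in leakage, so 560 becomes 560/0.992 ≈ 565. For 5/10/15% the share is (2 × 0.05²/3)/(0.10 × 0.90) = 1.9%, and 560 becomes about 571.

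**The case against.** The strongest reply is that this is a one-section condensation of a longer protocol, and that handling of centre is often left to the full document or the analysis plan. That would settle the matter if the article were silent on method. Here it names particular tests, and the t-test and chi-squared test as named do not accommodate centre, so the recommendation is to change a stated method.

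Other parts of the reply stand:
- **Centre differences are not shown.** No figure in the article gives leak rates or marker levels by centre. Common perioperative guidelines, the NSAID policy and a standardised web-based data system point to some uniformity, although none of these describes how breath, stool or plasma is collected.
- **The effect is small.** An AUC of 0.53 on its own would not pass for a useful predictor. The worry is the accumulation of false positives over many markers.
- **The logistic model is open.** A reader might infer that centre is ignored in the final algorithm. The article does not say so, because it lists no covariates.
- **Centre terms suit a transportable tool poorly.** A centre intercept has no value for a new hospital, and adjusting for centre can remove genuine case-mix signal. By-centre estimates would rest on about 51/3 = 17 leaks each.

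**Conclusion.** The point holds for the single-marker comparisons and the overall ROC area. As named, they take no account of centre in an unrandomised three-centre study, and they are biased when centre differences in leakage and marker level line up. Under the assumed 8/11.5/15% leak rates and shifts of 0.3 to 0.8 SD, the 5% test becomes one of about 8 to 23%. The spurious effect is d of about 0.07 to 0.15, against the design effect of 0.41. All of this rests on assumed centre values and equal centre sizes.

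Two stronger readings are not supported. One is that any centre difference will show up as a marker effect: equal leak rates or unaligned differences leave the error near 5%. The other is that the resulting algorithm must fail elsewhere: that would require the artefact to survive a logistic model whose covariates are not stated. The sample size is essentially unaffected. This is a worthwhile improvement at low cost; the article does not demonstrate that an error will occur.

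**What to change.** In the Statistical Analyses section:
1. Compare continuous markers between leak and non-leak patients in a linear model with centre as a covariate, in place of the plain t-test.
2. Compare dichotomous markers by the Mantel-Haenszel method stratified by centre, in place of the plain chi-squared test.
3. Beside the overall AUC, report a centre-adjusted AUC: compare leak with non-leak patients within the same centre and pool over centres.
4. As a sensitivity analysis, add centre to the logistic model and check that retained markers keep their association. Centre need not be part of the final risk tool.

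This is a change of wording, since the centre of each patient is known. It costs two extra parameters and slightly wider intervals, equivalent to roughly 5 to 11 patients on 560 under the leak rates assumed above. Separate estimates for each centre should not be relied on, because about 17 leaks per centre is too few for precision.

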**Conclusions:**

An estimated 8-10% of patients will develop AL following surgery, and they will be compared to non-leakage patients. The objectives of this study are twofold. The primary aim is to establish and validate a diagnostic algorithm for the pre-operative prediction of the risk of AL development using a combination of inflammatory, immune-related, and genetic parameters. Previously established risk factors and novel parameters will be incorporated into this algorithm, which will aid in the recognition of patients who are at risk for AL. Based on these results, recommendations can be made regarding the construction of an anastomosis or deviating stoma, and possible preventive strategies. Furthermore, we aim to develop a new algorithm for the post-operative diagnosis of AL at an earlier stage, which will positively reflect on short-term survival rates.

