### Study Objectives

The objectives of the Predictive Factors of Anastomotic Leakage after Colorectal Surgery (REVEAL) study are twofold. The primary aim of this study is to establish a risk assessment tool for the pre-operative prediction of the development of AL based on a combination of inflammatory, immune-related, and genetic parameters. This algorithm should enable surgeons to make an adequate estimation for every individual patient’s risk of AL, and will eventually aid in the decision-making process regarding the construction of anastomoses and deviating ostomies. In addition, this study aims to provide additional post-operative biomarkers for AL diagnosis at earlier stages, thereby reducing the clinical impact of this feared complication.

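### The abstract makes validating the pre-operative algorithm part of the primary aim, but the Study Objectives do not, and the analysis names no validation step and sets aside none of the roughly 51 leaks for one

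*Protocol article*

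**What the plan says.** Three places in the protocol article bear on this point.

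- **Abstract, Conclusions.** The primary aim covers development and validation: "The primary aim is to establish and validate a diagnostic algorithm for the pre-operative prediction of the risk of AL development". A second model is to come from the same cohort: "we aim to develop a new algorithm for the post-operative diagnosis of AL at an earlier stage".
- **Study Objectives.** The same primary aim appears without validation: "The primary aim of this study is to establish a risk assessment tool for the pre-operative prediction of the development of AL".
- **Statistical Analyses.** The sample size rests on one marker: "Based on an effect size of 0.41 (calculated with mean calprotectin levels and SD on day 1"). The resulting number is given as "with a power of 0.80 and a 95% confidence interval, the total sample size will be 560". The expected number of events is put at 51: "of whom an estimated 51 patients will develop AL". The methods listed are a normality test, t-tests, chi-squared tests, ROC curves for the studied markers and, for combining them, "To determine the most ideal combination of markers, logistic regression analyses will be performed". The section mentions no data split, resampling, shrinkage or second cohort, and does not say on which patients the combined model's AUC will be computed.

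**The concern.** None of the listed methods validates a prediction model. If validation is part of the primary aim, the analysis section does not deliver that part. If it is not, the abstract promises too much. The reader cannot tell which is meant.

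The gap matters because the number of events is already fixed. A logistic model that searches many candidates with about 51 leaks fits chance patterns along with real ones. Assessed on the patients who produced it, such a model looks more discriminating than it is, and its predicted risks are too spread out. The Study Objectives want an estimate of each patient's own risk, which is eventually to inform decisions on anastomoses and ostomies. Calibration therefore matters as much as AUC.

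**Working it through.** **1. The plan's own sample size.** Inputs from Statistical Analyses: effect size 0.41, power 0.80, and a 95% confidence level read as two-sided alpha 0.05. The 51 leaks in 560 (9.1%) imply about one leak per ten non-leaks.

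- Non-leaks = (1.960 + 0.842)² / 0.41² × (1 + 10) = 7.849 / 0.1681 × 11 = 513.6, so 514.
- Leaks = 514 / 10 = 51.4. Total about 565, against 560 stated.
- Power at 51 and 509: 0.41 × √(51 × 509 / 560) = 2.791, and Φ(2.791 − 1.960) = 0.797.
- Dropout: 560 × 1.05 = 588, as stated.

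The figure reproduces to within 1%. All 51 leaks are taken up by one two-group comparison, so none is reserved for validation.

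**2. Candidates named for the pre-operative model.**

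- Study Outline: six plasma markers (I-FABP, citrulline, calprotectin, smooth muscle protein 22, CRP, leukocytes), two genes (MBL, COX-2), SNAQ, the Malnutrition Universal Screening Tool, sarcopenia, atherosclerosis, the VOC pattern and the microbiome. That is 6 + 2 + 4 + 2 = 14.
- Introduction: male sex, neo-adjuvant chemotherapy, tumour size, smoking and steroids, which adds 5. NSAIDs are left out because they are withheld, and malnutrition because it is already covered.
- Total 19, so 51 / 19 = 2.7 leaks per candidate.

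The article gives no count of its own. Its plasma markers are examples, and VOCs and microbiome are each counted once here.

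**3. Size of the optimism.** Simulation with 51 leaks and 509 non-leaks, independent normal markers, three of them real at 0.41 (an assumption), and an unpenalised logistic fit. Each model was then applied to large new samples. Since the article states neither procedure, two were run: all candidates entered, and only those with univariable p < 0.05.

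| Candidates | Procedure | Apparent AUC | AUC in new patients | Calibration slope |
|---|---|---|---|---|
| 19 | all entered | 0.75 | 0.64 | 0.51 |
| 19 | screened | 0.71 | 0.66 | 0.75 |
| 10 | all entered | 0.73 | 0.66 | not computed |
| 10 | screened | 0.70 | 0.66 | not computed |
| 50 | all entered | 0.83 | 0.61 | not computed |
| 50 | screened | 0.74 | 0.64 | not computed |

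A slope of 1 means that predicted risks are spread correctly. At 0.5 the predicted log-odds are spread about twice as widely as they should be.

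**4. Can the cohort be split?** Halving it leaves about 25 leaks per half. Power at 0.41 falls to Φ(0.41 × √(25.5 × 254.5 / 280) − 1.960) = 0.51. The 95% half-width of an AUC between 0.65 and 0.75 grows from about 0.08 to about 0.12. Holding out one of the three centres leaves on average 51 / 3 = 17 leaks and a half-width of about 0.14 to 0.15.

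**5. Does the bootstrap correct the optimism?** With 20 candidates, three real, and the whole procedure repeated in each bootstrap sample:

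- screened: 0.71 corrected to 0.64, against 0.65 in new patients;
- all entered without penalisation: 0.76 corrected to 0.68, against 0.64 in new patients.

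The second correction is only partial, which argues for a short list and a penalised fit alongside the bootstrap.

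**The case against.** This is a condensed article. Resampling, shrinkage and candidate lists commonly sit in a full protocol or analysis plan, and neither is shown. Their absence alone would be no finding. That stands, and it limits the point to what the article does state: an aim worded in two ways, an analysis with no step matching the stronger wording, and a fixed number of events with none set aside.

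A reader might infer that the plan commits to reporting the combined model's AUC on its development data, so that the published accuracy is bound to be inflated. The text does not go that far. ROC curves are described for the studied markers, logistic regression follows in a separate sentence, and the assessment data are not specified. Same-data assessment is the natural reading because no other data are described, but the inflation remains conditional on it.

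Nor does the article say that t-tests or chi-squared tests decide which markers enter the model, so the screened results illustrate one possible procedure. Simulations with 30 or 100 candidates, or with pure noise, give larger gaps. The article supplies no such count, and its Introduction reports earlier signals for several markers. The 0.41 is itself a post-operative day 1 value, borrowed here for a pre-operative model. Finally, clinical use is described as eventual, so harm to decisions is less direct than it may seem.

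**Conclusion.** The point holds in a limited form. The abstract, the Study Objectives and the Statistical Analyses disagree on whether validation belongs to the primary aim, and the analysis as written contains none. If the model is selected, fitted and assessed on the same patients, AUC would be overstated by about 0.05 (screened) to 0.11 (all entered), with a calibration slope of about 0.75 and 0.5 respectively. Those sizes rest on 19 independent candidates, three real at 0.41, and about 51 leaks. With 10 to 50 candidates the overstatement runs from about 0.04 to 0.10 screened and 0.07 to 0.22 with all entered. The direction was the same in every scenario run. Should-fix, moderate confidence.

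**What to change.** Reconcile the primary aim in the abstract and the Study Objectives with the Statistical Analyses. In the latter, replace the sentence on the best combination with the following, for both algorithms:

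1. A short list of candidate predictors, fixed before the outcome data are analysed.
2. A penalised logistic fit.
3. The whole modelling procedure, any selection included, repeated in bootstrap samples.
4. Optimism-corrected AUC and calibration slope as the main results.
5. Performance by centre as supportive information only. About 17 leaks per held-out centre cannot carry a claim of validation.

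Call this internal validation. The alternative is to remove validation from the aim, so that the abstract matches the Study Objectives. A split sample should be avoided for the reasons in step 4 of the working.

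The cost is analysis wording, somewhat more analysis work and a lower reported AUC. No additional patients are needed.
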